### Ethics and dissemination

This trial has received ethical approval from Deakin University Human Research Ethics Committee (DUHREC; Ref: 2021–412). This study will be conducted in compliance with this protocol (Version 5, March 2023), which was registered (1 February 2022, last updated 26 April 2023) with the Australian New Zealand Clinical Trials Registry (ACTRN: ACTRN12622000168752). Any protocol changes will be communicated to the human research ethics committee, funder, and ACTRN. The protocol registration will be updated with any approved amendments, and protocol departures will be documented in any reports or manuscripts resulting from this study.

The study findings will be disseminated to academic audiences, via presentation at scientific meetings, and publication in peer-reviewed journals. For non-academic audiences, including participants, a lay summary will be published via a freely available blog on the research team’s website and disseminated via e-newsletter. Study findings will also be reported to the funding body. On the consent form, participants will be asked if they agree to use of their data should they choose to withdraw from the trial. Participants will also be asked for permission for the research team to share relevant anonymous data with researchers who want to conduct further analysis.

All intervention-related adverse events (SAE) reported spontaneously by a participant during sessions and phone interviews, or through routine inspection of data from online assessments will be reported to the DUHREC within 24 h and communicated to the project board. A data safety monitoring board has not convened because the intervention is considered low risk.

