#### Consent and procedure

The schedule of enrolment, intervention and assessment is detailed in Fig. 1. Study recruitment will be open for a maximum of 8 months (Fig. 2) or until the sample size (enrolled) is reached. Participation (from study entry to exit) will be for a duration of 6 months.

People with diabetes who are interested in participating will be directed to the study website to access the Plain Language Statement and provide informed consent. After providing consent, they will complete screening questions. Eligibility will be determined automatically based on responses. Those eligible will complete an online baseline assessment (T0) (hosted by Qualtrics™) and, will be randomly allocated to one of two study arms. Those who are ineligible will be informed immediately using an autogenerated message and provided with links to resources for mental health support.

Participants will be sent an email and SMS invitation with a link to the online follow-up assessment at 8 weeks (T1) and 6 months (T2) post-randomisation and allocation to the intervention or comparison group. The 8-week survey will be available for completion for 2 weeks. At the end of the first week, an email and SMS reminder will be sent to those who have not completed the survey. The 6-month survey will be available for completion for 3 weeks, with two reminders sent to non-responders at one and 2 weeks.

Participants will be e-mailed a $30 voucher on completion of the study (i.e. complete baseline, 8-week and 6-month follow-up assessments) as a token of appreciation, and to aid recruitment and retention.

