### Intervention

The intervention group will receive up to four LISTEN sessions (45–60 min each), facilitated by a diabetes HP via telehealth. Sessions will be offered weekly to allow participants sufficient time to implement their action plan (*homework tasks*) between sessions. The core of LISTEN provides participants with a 6-step approach to addressing problems related to their diabetes that are contributing to their distress (see Fig. 3). Participants receive information and worksheets to support them between sessions to plan meaningful and enjoyable activities. Where appropriate, HPs will provide participants with a letter of attendance to take to their General Practitioner (GP referral letter) to help initiate a conversation about accessing further support from a mental health professional.

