### Comparison group

The comparison group will continue with their usual care and will receive a weblink to a freely available NDSS online factsheet about diabetes distress (https://www.ndss.com.au/wp-content/uploads/fact-sheets/fact-sheet-diabetes-distress.pdf), as well as links to general mental health support (e.g. Beyond Blue). They will also receive a general letter if they would like to discuss their emotional well-being with their GP.

During the trial, regardless of trial arm allocation, participants will not be asked to change their medications or diabetes management plan.

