### Primary and secondary outcomes

All outcomes will be assessed pre-randomisation at baseline (T0), and post-randomisation at 8 weeks (T1) and 6 months (T2; primary endpoint).

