##### Intervention acceptability

Acceptability of LISTEN to participants in the intervention group, and their suggestions for improving sessions, will be explored using: (1) rating scales and open-ended questions at 8-week follow-up (T1); and (2) via semi-structured interviews with a random sample of 20–30 participants who undertake ≥ 1 LISTEN session). The random sample will be stratified to include a range of participants (e.g. by diabetes type, age, gender, number of sessions completed). The interview schedule is informed by the Theoretical Framework of Acceptability (TFA) [43] and adapted from a published interview exploring the acceptability of brief PST [21].

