### Planned analyses

Analysis of the primary outcome will be conducted on an intention-to-treat (ITT) basis, using repeated measures analysis of variance (ANOVA), or restricted maximum likelihood mixed-effects models (REML) [49]. The null hypothesis, that there is no difference in the primary outcome between the intervention and comparison groups (at T2), will be assessed using *p*-values for the fixed-effects for the associated covariates in each model, with a *p*-value < 0.05 deemed statistically significant. If participants have missing assessments at T2, the analysis of variance will be replaced by a mixed model analysis using the REML. A per-protocol set (PPS) will include only those participants who engage with all aspects of the study protocol and complete a minimum of one LISTEN session (intervention) or access the web-based resource (comparison) to be used for a sensitivity analysis of the primary endpoint. Secondary outcomes, including psychological distress (K10), general emotional well-being (WHO-5) and coping self-efficacy (CSES) will be analysed as per the primary outcome.

Qualitative data from semi-structured interviews will be de-identified, transcribed verbatim using a professional transcriber and imported into NVivo. Thematic analyses [50] will be used to explore and identify key themes about participant’s experiences of the LISTEN intervention and barriers to, and facilitators of, adoption and implementation.

There are no plans to conduct an interim analysis of the outcomes, as per the statistical analysis plan. Due to the low-risk nature of the intervention, we do not anticipate any harm associated with the intervention for participants, and thus have no stopping rules.

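### Adverse event counts under the stated rule are not comparable between arms: only intervention-related events qualify, and two of the three capture routes exist only in the LISTEN arm

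*Protocol article*

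**What the plan says.** The rule stands in Ethics and dissemination. It begins "All intervention-related adverse events (SAE) reported spontaneously by a participant during sessions and phone interviews" and continues "or through routine inspection of data from online assessments will be reported to the DUHREC within 24 h and communicated to the project board". It therefore names three routes: spontaneous report in a session, spontaneous report in a phone interview, and inspection of survey data. The word intervention-related governs all three.

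Other sections show who has access to each route.

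- Intervention section: "The intervention group will receive up to four LISTEN sessions (45–60 min each), facilitated by a diabetes HP via telehealth".
- Intervention acceptability section: acceptability is explored in the intervention group, partly "via semi-structured interviews with a random sample of 20–30 participants who undertake ≥ 1 LISTEN session".
- Comparison group section: "The comparison group will continue with their usual care and will receive a weblink to a freely available NDSS online factsheet about diabetes distress". Links to general mental health support and a letter for the GP are added. No sessions or interviews are described.
- Consent and procedure section: follow-up surveys go to participants "at 8 weeks (T1) and 6 months (T2) post-randomisation and allocation to the intervention or comparison group".
- Primary and secondary outcomes section: "All outcomes will be assessed pre-randomisation at baseline (T0), and post-randomisation at 8 weeks (T1) and 6 months (T2; primary endpoint").

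On the expected level of harm, Planned analyses says "we do not anticipate any harm associated with the intervention for participants" and gives this as the reason for having no stopping rules. Ethics and dissemination gives low risk as the reason for having no data safety monitoring board.

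**The concern.** A comparison of harm between randomised arms needs the same definition of an event and the same opportunity to detect it in each arm. The stated rule provides neither. The definition depends on the intervention that only one arm receives, and two of the three routes run through contact that only that arm has.

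The two faults do not cancel. Unequal opportunity to report inflates the LISTEN count. The relatedness condition, read literally, holds the usual-care count near zero whatever happens to those participants. An excess in the LISTEN arm could be an artefact of capture, and a count of zero would not be evidence of safety, because there is no comparator.

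This matters because the trial is meant to inform a decision on implementation at scale, and its participants are selected for elevated diabetes distress. Low risk is the stated reason for having no monitoring board and no stopping rules, and the events recorded under this rule cannot test it.

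**Working it through.** **Step 1. Match each route to the arms that have it.** The plan states no figure on this point, so there is nothing to reproduce.

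| Route | LISTEN | Usual care | Where stated |
|---|---|---|---|
| Report during a session | yes, up to four sessions | no | Intervention; Comparison group |
| Report during a phone interview | yes, 20–30 people | none described | Intervention acceptability |
| Inspection of online assessments | yes | yes | Consent and procedure; Primary and secondary outcomes |

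Two of the three routes are open to one arm only. With N = 454 randomised 1:1 there are 454/2 = 227 per arm. The interviews would therefore reach 20/227 = 9% to 30/227 = 13% of the LISTEN arm and nobody in usual care. The shared route is also not fully identical: at T1 the acceptability ratings and open-ended questions concern the intervention group only.

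**Step 2. Apply the relatedness condition.** Usual-care participants receive no LISTEN session, so an event attributed to the intervention is close to impossible for them by definition. The expected usual-care count is about 0 at any true event rate. The shared third route does not repair this, because the same condition applies to it.

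**Step 3. Illustrate the effect of unequal capture alone**, with the relatedness condition set aside. Recorded events per arm = 227 × true rate × probability of detection. The true rate is taken as equal in both arms. All rates and detection probabilities here are assumptions; the document gives none.

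| Detection, LISTEN / usual care | Recorded at 5% true rate | Recorded at 10% true rate | Ratio |
|---|---|---|---|
| 50% / 50% | 5.7 / 5.7 | 11.4 / 11.4 | 1.0 |
| 75% / 50% | 8.5 / 5.7 | 17.0 / 11.4 | 1.5 |
| 90% / 50% | 10.2 / 5.7 | 20.4 / 11.4 | 1.8 |
| 75% / 25% | 8.5 / 2.8 | 17.0 / 5.7 | 3.0 |

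With no true difference, the unequal-detection rows make LISTEN look 1.5 to 3 times worse.

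**Step 4. Precision of a deterioration outcome defined the same way in both arms.** The Sample size section plans for 113 per arm after attrition. For the same rate p in both arms, the 95% CI half-width of the risk difference is 1.96 × √(2p(1 − p)/113).

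- p = 5%: 1.96 × √(2 × 0.05 × 0.95/113) = 0.057, about ±6 points.
- p = 10%: 1.96 × √(2 × 0.10 × 0.90/113) = 0.078, about ±8 points.
- p = 20%: 1.96 × √(2 × 0.20 × 0.80/113) = 0.104, about ±10 points.

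These rates are also assumptions. The half-widths describe the proposed outcome; they do not measure the size of the fault.

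**The case against.** The strongest objection is that the sentence is a notification rule. It sits under ethics and says what goes to the ethics committee within 24 hours. It does not say that other events go unrecorded, or that these counts will be compared by arm. Restricting urgent notification to related events need not decide how harm is tabulated. This stands in part, and it is why the notification rule should stay as it is. But it is the only adverse event rule in the document. If events are gathered only under it, no later analysis can make the counts comparable.

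A reader might infer that the trial cannot compare harm between arms at all. The document does not support that. PAID at T2 is the primary outcome, and K10, WHO-5 and coping self-efficacy are analysed in the same way, so an average worsening under LISTEN would show in a randomised comparison. What averages do not show is whether some participants deteriorate while the mean improves.

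A reader might also infer that events come mainly from sessions and interviews. The protocol does not rank its routes, and the third covers both arms. Nor should the three to four hours of sessions (4 × 45 to 4 × 60 min) be read as time spent eliciting harm; that is therapy time, with spontaneous reports only.

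Finally, the absence of a trigger threshold, a harms table or separate definitions is not an error in itself. An article commonly leaves these to the full protocol or the analysis plan, neither of which is shown. The point rests on the rule that the article does state.

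**Conclusion.** The point holds for adverse event counts. As stated, the rule restricts events to those related to an intervention that one arm does not receive, and two of its three routes exist only in the other arm. The resulting counts are not comparable between arms and cannot support or refute the low-risk premise. Under the assumed detection rates, unequal capture alone gives a spurious ratio of 1.5 to 3; the relatedness condition leaves practically no comparator count. The size of the actual distortion is unknown, because the document gives neither event rates nor detection rates.

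The conclusion assumes that the text is complete on who is interviewed, since the flow figures are not visible. It does not touch the effectiveness analysis. It is a cheap improvement to harm reporting and does not undermine the trial.

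Separately, the opening of the rule puts the abbreviation for serious adverse events after the words for adverse events in general. It is unclear whether all intervention-related events or only serious ones are meant, and the wording must be reconciled.

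**What to change.** 1. Leave the 24-hour notification to the ethics committee unchanged.
2. For reporting harm by arm, do not make relatedness a condition for counting; record it as an attribute of the event if wanted.
3. Inspect online assessments in both arms by the same written criterion, using only items that both arms complete. List events reported in sessions or interviews separately, marked as available for the LISTEN arm only.
4. Add one prespecified deterioration outcome: the proportion whose PAID or K10 worsens from T0 to T1, and from T0 to T2, by an amount that the investigators fix before seeing outcome data by arm. Report the between-arm risk difference with its 95% CI.
5. Reconcile the adverse event and serious adverse event wording.

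The cost is a few sentences in the protocol and analysis plan and one extra table. PAID and K10 are already collected in both arms at all three time points, so no new data are needed. The drawback is modest precision, about ±6 to ±10 points over the assumed rates. The new outcome also depends on survey completion, for which the plan allows 50% attrition, so the number assessed in each arm should be shown beside the proportions.

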### Stakeholder consultation

We have consulted with key stakeholders (adults with type 1 and type 2, diabetes HPs and representatives from diabetes organisations) to refine the study methodology, including the LISTEN intervention and LISTEN training of diabetes HPs. Further input will be sought from people with diabetes throughout the study; their roles will include advising on recruitment materials, making recommendations for implementation and scaling, and providing input into further refinements to the delivery of LISTEN and HP LISTEN training.

## Discussion

In Australia and internationally, there are a lack of real-world services that provide early intervention to enhance positive coping with the ongoing burden of living with diabetes. LISTEN aims to upskill diabetes health professionals to provide such early intervention, using structured, evidence-based, problem-solving skills and strategies, to meet the needs and preferences of people with diabetes. This trial will generate robust clinical outcomes data of the effectiveness and cost-effectiveness of LISTEN. Furthermore, our process evaluation will yield data on the barriers to, and facilitators of, the implementation and sustainability of LISTEN in practice, including evidence-based, pragmatic strategies to ensure high fidelity and sustainable program delivery. The findings will inform the implementation of LISTEN as a sustainable real-world service, designed to have an immediate and lasting positive impact on the emotional and mental health of Australians with diabetes.

## Trial status

The study protocol was registered before inclusion of the first participant on https://www.anzctr.org.au. Recruitment for this trial commenced in August 2022 and will continue until the target sample size is reached, which is anticipated in April 2023. We plan to complete the collection of 6-month follow-up data by October 2023.

The study protocol date: Initial approval December 2021; Current version 5, approved April 26, 2023.

## Data Availability

The research team members at the Australian Centre for Behavioural Research in Diabetes/Deakin University will have access to the trial dataset that is deidentified once the trial is completed. Data are available upon reasonable request. The final dataset will be available for researchers who are interested in the related topics after the research team has disseminated the main findings of the research aims. Permission from the lead investigator is required for any publications and dissemination effort.
